### Recruitment {15}

Participants are recruited at the Rheumatology department of various hospitals. Currently, we aim at the participation of seven Dutch centres in this trial.

## Assignment of interventions: allocation

### Sequence generation {16a}

Participants will be randomized in a 1:1 ratio to either the continuation T2T or T2S discontinuation strategy. Participants will be randomized by the research physician using a computerized randomization procedure with variable block sizes. No stratifications are made since no strong predictors of flare were found in the previous literature

### Concealment mechanism {16b}

Opaque-sealed envelopes are used to conceal the allocation sequence prior to the randomization of each patient.

### Implementation {16c}

Randomization blocks are generated by an online programme and have variable block sizes to achieve the intended allocation ratio and to prevent the allocation from being predictable for the treating physician..

## Assignment of interventions: blinding

### Who will be blinded {17a}

Patients, research nurses and physicians will not be blinded for treatment allocation. Analyses will be performed blinded for treatment groups. Due to the nocebo effect, patients (and treating physicians) in the discontinuation treat-to-avoid-symptom group could expect more gout flares after ULT cessation, and therefore the number of gout flares could be higher in this group. However, validated gout flare criteria are used to determine whether or not an event is deemed as a gout flare or not. If in doubt an out-patient visit is scheduled for a clinical examination by a (research) physician

### Procedure for unblinding if needed {17b}

Does not apply.

## Data collection and management

### Plans for assessment and collection of outcomes {18a}

Regular visits are planned at baseline, month 12 and month 24 (Fig. 3). Digital or paper questionnaires are sent monthly (gout flare questionnaire) and three monthly (set of questionnaires). The Health Assessment Questionnaire (HAQ)-II, iMTA Productivity Cost Questionnaire (iPCQ), iMTA Medical Consumption Questionnaire (iMCQ), EuroQol-five-Dimensional Questionnaire with Likert response(EQ-5D-5L) are all validate questionnaires. Based on the advice of the OMERACT for study outcomes for acute gout we included the HAQ-II. The use of the EQ-5D-5L, iPCQ and iMCQ for this study was requested and granted.

**Fig. 3 Fig3:**
[figure not shown]
SPIRIT: trial visits and assessments

### Plans to promote participant retention and complete follow-up {18b}

Firstly, a telephone call is scheduled 2 weeks after ULT cessation in the T2S discontinuation group to make sure ULT is indeed stopped. Secondly, a process database is maintained to make sure questionnaires and outpatient visits are scheduled on time and have been completed. If a questionnaire has not been returned on time (digital or by post), the participant is requested by email or telephone call, to complete it as soon as possible. Also, participants have a direct work phone number of the physician-researcher so that contact can be made if they are experiencing a gout flare or have any questions. If participants are lost to follow-up or withdraw consent, the data that has been collected up to that time will be used

### Data management {19}

Patient, disease, and treatment characteristics are extracted from the electronic health record and encrypted entered and stored in the data management system Castor EDC. Questionnaires are sent and answers are locked in the database using automated sending and data saving through Castor EDC. If patients receive their questionnaires by post, the answers are entered manually and locked afterwards. All paper questionnaires are stored at the concerned study site. A data management plan is created in line with the General Data Protection Regulation, which can be viewed upon request.

### Confidentiality {27}

The collected data will be coded and stored by the rules of good clinical practice. Personal data will be handled in compliance with the Dutch Act on Implementation of the General Data Protection Regulation (Algemene Verordering Gegevensbescherming, AVG). Data of participants will be handled confidentially. A unique study code will be assigned to each participant. The code consists of an abbreviation for the study centre and a number. Patients’ name and contact details will be saved together with the unique patient code in the process database (ID-log) which will be secured with a password. The password is available to the coordinating investigator, principal investigators, and study team members when this is necessary to execute their tasks and study monitor.

### Plans for collection, laboratory evaluation and storage of biological specimens for genetic or molecular analysis in this trial/future use {33}

The blood samples that are collected for regular care throughout the study will not be stored and will be handled according to local laboratory agreements that conform to regular care. Blood samples obtained for the biobank will be stored for future research and can be stored for a maximum of 15 years. Written informed consent is obtained to do so.

## Statistical methods

### Statistical methods for primary and secondary outcomes {20a}

#### Primary outcome

For superiority testing data is handled primarily by intention-to-treat analyses. Analyses will be conducted using the two proportion *z* test. Results will be interpreted with a *p*-value of *P* <0.05 as significant.

#### Secondary outcomes

Only when superiority cannot be demonstrated, non-inferiority testing will take place exploratory of the treat-to-symptom strategy compared to the treat-to-target strategy by calculating a confidence interval using the Miettinen and Nurminen method [30].The between-group difference in the incidence (cumulative incidence and incidence density rate) of gout flares during the follow-up period of 24 months.

Cumulative flare incidence is expressed as a proportion of the number of patients experiencing a flare at any time during the follow-up period. This is calculated separately for both groups and will be described by means of descriptive statistics as *n* (%). These proportions are compared using a chi-squared test or Fisher’s exact testThe proportion of participants that require reintroduction of ULT in the T2S group during the 24-month follow-up period.

The proportion of the number of patients in the T2S group in which the ULT is restarted will be expressed as n (%).The between-group difference in SU change during the total follow-up time and particularly at baseline and at the end of follow-up at 24 months.

Serum urate at baseline serum urate, 2 weeks after ULT discontinuation, month 12 and month 24 will be described as mean and 95% confidence intervals (CI). The difference from baseline measurement will also be described by the mean and 95% CI. A difference between the two groups will be compared with an independent *t*-test or Mann-Whitney test.To evaluate the between-group difference in Patient-Reported Outcome Measures (PROMs), by three monthly analysing the EQ-5D-5L questionnaire, functioning by using the Health Assessment Questionnaire Disability Index (HAQ-DI), numeric rating scale (NRS) for pain and NRS global health

Descriptive statistics in the form of mean and 95% CI will be used. The difference from baseline will also be presented using the mean and 95% CI. The difference in change in EQ-5D-5L, HAQ-DI, NRS pain and NRS global health between the groups will be analysed by an independent t-test or Mann-Whitney test.To assess the between-group difference in types and frequency of adverse events, with a special focus on change in renal function (CKD-EPI) and incidence of cardiovascular events during the follow-up period of 24 months.

During the study, adverse events are registered using the Common Toxicity Criteria for Adverse Events. The results will be presented by using descriptive statistics. The occurrence of adverse events between the groups is compared using a chi-squared test or Fisher’s exact test.To assess the between-group difference in use of ULT and flare medication (colchicine, NSAIDS and/or glucocorticoids).

Per group, the proportion of patients using flare medication, restarting ULT or experiencing a ULT increase/decrease will be described as *n* (%). The difference between the groups will be analysed using a chi-squared test or Fisher’s exact test.To assess the between-group difference in prescribed medication compared with refill rates and self-reported adherence during the follow-up period of 24 months.

First, it will be examined per group whether the self-reported medication use corresponds with the refill adherence information from the pharmacy/LSP, this is described by means of *n* (%). Then the difference between the two treatment groups will be compared by using a chi-squared test or Fisher’s exact test.To assess predictors for successful ULT cessation in de T2S strategy group including clinical, radiological, and immunological, variables.

Regression analyses will be used to exploratory identify possible predictive variables for unsuccessful withdrawal of uric acid-lowering medication. This will include radiological, biochemical, patient and disease characteristics.

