#### Secondary objectives

To exploratory assess non-inferiority (only when superiority cannot be demonstrated) of the treat-to-symptom strategy compared to the treat-to-target strategy.To assess the between-group difference in the incidence (cumulative incidence and incidence density) of gout flares during the follow-up period of 24 months according to gout flare criteria [23].To assess the proportion of participants that require reintroduction of ULT in the T2S discontinuation strategy group.To assess the between-group difference in the use of ULT and gout flare medication (anti-inflammatory medication).To assess predictors for successful ULT cessation in the T2S discontinuation strategy group including clinical, radiological, immunological, and genetic variables.To evaluate the between-group difference in Patient-Reported Outcome Measures, by three monthly analysing the 5-level EuroQol-5 domains (EQ-5D-5L) questionnaire, functioning by using the Health Assessment Questionnaire Disability Index (HAQ-DI), numeric rating scale (NRS) for pain and NRS global health.To assess the between-group difference in types and frequency of adverse events, with a special focus on change in the renal function defined by Glomerular Filtration Rate Chronic Kidney Disease – Epidemiology Collaboration (GFR-CKD-EPI) and incidence of major adverse cardiovascular events (defined as arrhythmia, non-fatal stroke, non-fatal myocardial infarction, (hospitalization for) acute coronary syndrome, cardiovascular hospitalizations and cardiovascular death) during the follow-up period of 24 months. For the MACE there is a special interest in the first 3 to 6 months after ULT cessation and reintroduction of ULT in the T2S group.To assess the (between-group) difference in prescribed medication compared with refill rates during the follow-up period of 24 months.To assess the incremental cost-effectiveness of a T2T ULT continuation strategy compared to a T2S ULT discontinuation strategy.

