## Interventions

### Explanation for the choice of comparators {6b}

Since we hypothesize that a T2T ULT continuation strategy is superior compared to a T2S ULT discontinuation approach in gout patients in remission, the control group is the T2S discontinuation strategy group.

In the T2S strategy, ULT is tapered to stop and restarted in case of recurrent or persistent flaring or the emergence of tophi. Thereafter, (re)treatment is T2T, thus also based on serum urate levels. ULT is tapered to stop in a maximum of 6 weeks based on ULT dosage at baseline (Table 2). A taper strategy was recommended over a direct stop strategy by the regional medical review board. This was based on studies that showed associations between cardiovascular events and the start/stop of ULT, presumably due to rapid serum urate changes. Tapering is expected to prevent rapid serum urate changes and thereby serious cardiovascular adverse events. Two weeks after ULT cessation an extra blood sample is obtained to check for any changes in blood counts and kidney and liver function. Serum urate levels will most likely increase, but this is not acted upon as in the T2S discontinuation strategy, ULT treatment is based only on symptoms. A telephone consult is planned three weeks after ULT cessation to verify that ULT has indeed been stopped, to discuss the tapering process and to discuss the blood results.

**Table 2 Tab2:** Tapering schedules of urate-lowering therapies in the treat-to-avoid-symptoms discontinuation group

**Baseline dose**	**First tapering step at baseline**	**Second tapering step 2 weeks from baseline**	**Third tapering step 4 weeks from baseline**	**Fourth tapering step 6 weeks from baseline**

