### Criteria for discontinuing or modifying allocated interventions {11b}

Tapering or stopping of ULT in the T2T ULT continuation group (intervention group) will only be done when serum urate level drops below 0.20mmol/l, side effects, or toxicity occurs. As patients included in the study have been stable on ULT for at least 12 months, it is expected that few changes in ULT will have to be made during the study period.

In the T2S ULT discontinuation group (control group), ULT is restarted in case of recurrent flaring or at the emergence of tophi. However, if a first gout flare is severe, an immediate restart of ULT is an option. Finally, if any other unforeseen circumstances occur and this can be linked to the ULT discontinuation period, the re-introduction of ULT can be considered.

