Only when superiority is not shown, non-inferiority (NI) of T2S compared to T2T will also be tested (using a NI margin of 8%, based on the NNH of a maximum of 12). Assuming 278 evaluable patients, point estimates for the primary outcome of 0.04 and 0.05 in the intervention and control group, and one-sided alpha of 5%, the power for proclaiming non-inferiority will be around 87%. However, we are aware of a higher risk of a false-positive result, also because this secondary analysis uses an opposite hypothesis of the original superiority hypothesis, therefore the non-inferiority analysis is considered an exploratory secondary analysis.

The NI margin is just like the difference in the superiority analysis based on the notion — developed together with patient partners — that a lower limit of NNH of 12 (not obtaining or loss of gout remission) balances nicely with the numbers needed to benefit of between 2 and 4 of not needing daily ULT pills for up to 2 years. In other words, a treatment effect smaller than an 8% point difference is not considered worthwhile compared to the burden of taking the medication.

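### The planned tests on ULT decrease and restart mostly compare the allocation with itself, and no planned measure directly estimates how much ULT each strategy uses

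*Protocol article*

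**What the plan says.** The Secondary objectives list a between-group difference in the use of ULT and of flare medication. Under Statistical methods {20a}, Secondary outcomes, this becomes, for each arm, the share of patients who take flare medication and the share "restarting ULT or experiencing a ULT increase/decrease will be described as" n (%). The next sentence fixes the test: "The difference between the groups will be analysed using a chi-squared test or Fisher’s exact test".

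Four other places bear on what that comparison can show:

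- **T2S arm, section {6b}:** "In the T2S strategy, ULT is tapered to stop and restarted in case of recurrent or persistent flaring or the emergence of tophi". Also "ULT is tapered to stop in a maximum of 6 weeks based on ULT dosage at baseline", with the steps in Table 2.
- **T2T arm, section {11b}:** tapering or stopping is limited to serum urate below 0.20 mmol/l, side effects or toxicity, and "it is expected that few changes in ULT will have to be made during the study period".
- **Restart, Secondary outcomes {20a}:** a separate item reports the T2S patients who restart as n (%), with no between-group test.
- **Margin, Sample size {14}:** the 8-point threshold is justified by setting a number needed to harm of 12 against "numbers needed to benefit of between 2 and 4 of not needing daily ULT pills for up to 2 years".

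**The concern.** The objective asks how much ULT each strategy uses. The measure counts events in a patient's ULT course, and the two arms are not exposed to those events in the same way. T2S patients have a decrease because they were randomised to one. T2T patients have nothing to restart unless they stopped outside the plan. An increase can mean building back to the previous dose after a restart in T2S, or intensification for urate or flares in T2T.

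Two things are at stake. A very small P value on decrease could be reported as a finding about ULT use when it only shows that the allocation was followed. And the trial weighs loss of remission against patients spared daily ULT. The primary outcome gives the harm side as a between-group estimate. The benefit side has none: neither the proportion off ULT nor the time off ULT is listed.

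**Working it through.** **Arm size.** Sample size {14} gives 0.04 v 0.12, one-sided alpha 0.05 and power 0.80. The unpooled formula gives n per arm = (1.645 + 0.842)² × (0.04×0.96 + 0.12×0.88) / 0.08² = 6.183 × 0.144 / 0.0064 = 139.1. This agrees with the stated 278 analysable patients, so 139 per arm is used below. The article gives no rate for ULT changes in either arm; every such rate here is an assumption, shown as a range.

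**Decrease.** If every T2S patient follows Table 2, the T2S count is 139/139. Two-sided Fisher's exact test:

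| T2S with decrease | T2T with decrease | P |
|---|---|---|
| 139/139 | 7/139 (5%) | 2e-71 |
| 139/139 | 14/139 (10%) | 2e-63 |
| 139/139 | 42/139 (30%) | 2e-41 |
| 111/139 (80%) | 42/139 (30%) | 5e-17 |

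Even at true rates of 80% v 50%, the power of the test is 0.9995. The result is fixed by design, with or without full adherence.

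**Restart.** Take T2T as 0%, since only a patient who stopped can restart. Fisher's test needs 6/139 v 0/139 (P = 0.030); 5/139 v 0/139 gives P = 0.060. Power by assumed T2S restart rate:

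| T2S restart rate | 2% | 4% | 5% | 8% | 12% |
|---|---|---|---|---|---|
| Power | 0.06 | 0.48 | 0.70 | 0.97 | 0.9995 |

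Significance is therefore conditional on the T2S rate. The fault is that almost nobody in T2T is at risk of the event, so the contrast is uninformative whatever P turns out to be.

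**Increase.** Power by assumed rates in the two arms:

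| Rates | 5% v 5% | 10% v 5% | 15% v 5% | 20% v 10% | 10% v 0% |
|---|---|---|---|---|---|
| Power | 0.02 | 0.27 | 0.76 | 0.60 | 0.996 |

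This comparison is not predetermined. Its weakness is definition. Section {6b} describes a restart as a stepwise build-up to the baseline dose, whereas section {11a} describes intensification in T2T for serum urate above 0.36 mmol/l or flares. Nothing says whether the first counts with the second.

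**Benefit behind the margin.** A number needed to benefit of 2 to 4 is a risk difference of 1/2 = 50% to 1/4 = 25% spared ULT. If no T2T patient is off ULT and all T2S patients stop, that means 50% to 75% of T2S patients restart. The planned T2S restart proportion gives this share by subtraction. It says nothing about time off ULT, counts patients who never stopped as not restarted, and is not a between-group difference.

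**What a direct estimate would give.** With T2T at 0%, the standard error is √(p(1−p)/139). For p = 0.25 it is 0.0367: 95% CI 17.8% to 32.2%, or a number needed to benefit of 3.1 to 5.6. For p = 0.50 it is 0.0424: 95% CI 41.7% to 58.3%, or 1.7 to 2.4. Either can be set beside the planned 2 to 4.

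**The case against.** The strongest reply is that this is a small matter of wording in a condensed article.

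- **Derivation rules.** Whether the assigned taper counts as a decrease may be settled in the full protocol or SAP, and the Abstract's label (reintroduction or adaptation of ULT) could mean departures from the assigned regimen. This is possible. But the article does state the measure, the groups and the test, and nothing in it excludes the taper.
- **Restart scored as increase.** The sentence lists restart separately, so counting a restart as an increase too is an inference. This stands; the point here is only that the text leaves it open.
- **Benefit already visible.** T2T patients stop only for narrow reasons, so the complement of the T2S restart proportion is close to the between-arm difference in patients off ULT. This largely stands for the proportion, subject to the limits shown above.
- **The replacement also follows allocation.** True of its P value: 35/139 and 70/139 v 0/139 give about 5e-12 and 1e-26. That is why the new measures should be estimates with intervals and not tests.
- **No decision hangs on it.** The number needed to benefit was a prior judgement made with patient partners, and the article does not promise to revisit it. This stands and limits the weight of the point.

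A reader might infer that all three ULT comparisons are bound to be significant. The documents do not support that: it holds for decrease, depends on the T2S rate for restart, and fails for increase. It would hold for the whole only if the sentence defined one composite of any ULT change, and the text does not say so. A reader might also infer that the ULT-free benefit goes wholly unmeasured; the separate T2S restart item shows otherwise.

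**Conclusion.** The point holds in limited form. The stated method does not measure the stated objective. The decrease comparison is decided by allocation (P of 5e-17 or smaller in every scenario tabulated), the restart comparison has almost no one at risk in T2T, and increase mixes two kinds of event unless it is defined. The share spared ULT, on which the 8-point margin leans, can be recovered only approximately and from one arm.

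This rests on reading decrease to include the Table 2 taper, on about 139 patients per arm, and on assumed ULT-change rates. The flare-medication comparison in the same sentence is sound. The primary outcome, its test and the sample size are unaffected. It should be corrected, but it does not threaten the trial's main conclusion.

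**What to change.** As a secondary analysis:

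1. Drop the between-group tests on ULT decrease and ULT restart. Keep restart as the T2S-only n (%) already planned.
2. Report by arm the proportion not using ULT at month 24, with the risk difference and its confidence interval, and set its inverse beside the planning value of 2 to 4.
3. Report by arm the months off ULT out of 24. Present this and item 2 as estimates and not as significance tests.
4. For the analysis, count as an increase only a dose above the patient's own baseline dose or an added ULT, in both arms.

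The cost is revised wording and slight extra analysis work. Treatment, visits and data collection do not change: section {11c} collects medication use by three-monthly questionnaire, the cost analysis records type and dose at visits, and section {20a} already compares self-reported use with pharmacy refill data.

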### Intervention description {11a}

In the intervention group, ULT treatment will be continued using a T2T strategy in which ULT is dosed based on serum urate levels as well as symptoms. Since visible tophaceous gout at baseline is an exclusion criterion for participation, we chose a uniform treatment target of <0.36mmol/l for the T2T ULT continuation group, with a lower limit of 0.20 mmol/l (0.34 mg/dl). Patients who have had tophi previously are treated using the treatment target of serum urate <0.36 mmol/l. The lower limit was chosen due to suggestions of a correlation between low uric acid and neurodegenerative diseases [27, 28]. Therefore, in case serum urate level drops below 0.20 mmol/l during follow-up, a dose reduction is considered and, in case serum urate level becomes higher than 0.36 mmol/l and/or gout flares occur ULT treatment is intensified. This latter can be done by increasing dosage, combing or switching ULT until the serum urate target and/or clinical remission are achieved again. When side effects occur, ULT will be switched as well

All treatment decisions are ultimately at the discretion of the patient and the treating physician.

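### The adherence comparison tests agreement between self-report and refills across arms; that is not adherence, and for ULT it partly reflects the randomised difference in exposure

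*Protocol article*

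**What the plan says.** The Secondary objectives {7} of the protocol article state the aim as "To assess the (between-group) difference in prescribed medication compared with refill rates during the follow-up period of 24 months". Statistical methods {20a}, Secondary outcomes, repeats it with an addition: "between-group difference in prescribed medication compared with refill rates and self-reported adherence during the follow-up period of 24 months".

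The analysis under that heading has two steps. The first is "First, it will be examined per group whether the self-reported medication use corresponds with the refill adherence information from the pharmacy/LSP", described as n (%). The second is "Then the difference between the two treatment groups will be compared by using a chi-squared test", with Fisher's exact test as the alternative. The second step does not name its variable; the n (%) just before it is the natural candidate. Nothing limits the comparison to patients or periods with ULT prescribed.

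ULT exposure differs between the arms by allocation. For control, Explanation for the choice of comparators {6b} says: "In the T2S strategy, ULT is tapered to stop and restarted in case of recurrent or persistent flaring or the emergence of tophi", and "ULT is tapered to stop in a maximum of 6 weeks based on ULT dosage at baseline". For the intervention arm, Intervention description {11a} says: "In the intervention group, ULT treatment will be continued using a T2T strategy".

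**The concern.** The objective needs a comparison of what was dispensed, or taken, with what was prescribed. The stated analysis compares what patients say with what the pharmacy dispensed. Two problems follow.

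- **Agreement is not adherence in either arm.** A T2T patient who admits taking nothing and collects nothing is scored as agreeing. So is a T2S patient who openly keeps taking and collecting ULT. Both have left the allocated strategy.
- **For ULT the arms are not on the same footing.** A T2S patient who is truly off ULT has none to report and none to collect, so the records agree almost automatically. A T2T patient's records must match over 24 months of use. Part of any arm difference therefore comes from how many patients are on ULT.

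At stake is the reading of one secondary outcome. In an open-label strategy trial it helps to know how well T2T patients obtained their prescribed ULT, and how many T2S patients went on obtaining it after the planned stop. The stated test answers neither question directly.

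**Working it through.** **Setting the texts side by side**

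| Element | Objective | Stated analysis |
|---|---|---|
| Reference | prescribed medication | self-reported use |
| Compared with | refill rates | pharmacy/LSP refill information |
| Summary | between-group difference | n (%) agreeing, chi-squared or Fisher's exact |
| Restricted to prescribed periods | not stated | not stated |

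Prescription drops out between the two columns. That is the core of the point and needs no arithmetic.

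**How large the artefact could be**

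The documents give no figure for this analysis, so the following only illustrates it.

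Inputs:
- n = 139 per arm, from 278 analysable patients randomised 1:1 (Sample size {14}). This figure reproduces with unpooled variance: (1.645 + 0.842)² × (0.04×0.96 + 0.12×0.88) / 0.08² = 139.1 per arm.
- c = agreement among ULT users, the same in both arms. Not in the documents; taken as 70%, 80% and 90%.
- Agreement among T2S patients off ULT: assumed 98%.
- q = share of T2S off ULT. Not given directly. Sample size {14} mentions numbers needed to benefit of 2 to 4 for not needing daily ULT; read as 1/4 to 1/2, this gives 25–50%. That is an interpretation, so 60% and 80% are shown as well.
- Two-sided 5% test (assumed).

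Formulas:
- Agreement in T2T: p_T = c.
- Agreement in T2S: p_S = 0.98q + c(1 − q).
- Gap: d = p_S − p_T = q(0.98 − c).
- Rejection probability: Φ[(d − 1.96·se0)/se1] + Φ[(−d − 1.96·se0)/se1]. Here se0 = √(2p̄(1 − p̄)/n), p̄ is the mean of p_T and p_S, and se1 = √([p_T(1 − p_T) + p_S(1 − p_S)]/n).

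Worked case, c = 0.70 and q = 0.50:
- p_S = 0.49 + 0.35 = 0.84, so d = 0.14 and p̄ = 0.77.
- se0 = √(2×0.77×0.23/139) = 0.0505.
- se1 = √((0.2100 + 0.1344)/139) = 0.0498.
- (0.14 − 1.96×0.0505)/0.0498 ≈ 0.82, giving 80%; the second term is negligible.

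All cases (T2S agreement, then rejection probability):

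| User agreement c (= T2T) | q = 25% | q = 50% | q = 60% | q = 80% |
|---|---|---|---|---|
| 70% | 77.0%; 26% | 84.0%; 80% | 86.8%; 93% | 92.4%; 99.8% |
| 80% | 84.5%; 17% | 89.0%; 55% | 90.8%; 72% | 94.4%; 95% |
| 90% | 92.0%; 9% | 94.0%; 23% | 94.8%; 33% | 96.4%; 56% |

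In every cell ULT users behave identically in the two arms. The gap, 2 to 22.4 percentage points, comes only from the mix of patients on and off ULT.

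**The case against.** A fair defence has five parts.

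1. **Agreement in T2S is not fully automatic.** There are taper weeks, restarts and possible undeclared use. A patient who reports having stopped while ULT is still dispensed shows up as disagreeing. Strategies to improve adherence {11c} counts anti-inflammatory drugs as monitored medication too, and a T2S patient off ULT may use those. This stands: the near-automatic part is limited to ULT in patients truly off it, and the measure keeps value as a check on self-report.
2. **The heading in {20a} includes self-reported adherence**, so comparing self-report with refills is part of the aim, and the two steps could be read as a validity check followed by an unnamed adherence comparison. That reading is possible but less natural, because no adherence variable is defined for the test.
3. **The size is uncertain.** A reader might infer that the trial is bound to report a significant artefact. The documents do not support that: at 25–50% off ULT and 90% user agreement, rejection is only 9–23%. Nor does the 47% ULT adherence cited in the Background imply low agreement. It is adherence in earlier work, and poorly adherent patients can still report accurately.
4. **Other exposure data are planned.** Restarts, ULT dose changes and serum urate by arm (two weeks after stopping, month 12, month 24) are to be reported, and a telephone call checks that ULT was stopped. A reader might infer that the primary result would be left without exposure information; that goes too far. These data do not, however, replace refill coverage.
5. **The article is condensed** and the full protocol is not shown. Definitions and thresholds may well sit there. But an analysis that is stated and does not match its objective is not merely omitted detail.

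**Conclusion.** The point holds for a secondary outcome. On the natural reading of {20a}, the test compares self-report/refill agreement between arms, whereas the objective concerns prescribed against refilled medication. Agreement does not measure adherence, and for ULT the between-arm contrast is partly created by allocation.

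The artefact cannot be sized from the documents. Under the stated assumptions, spurious rejection lies between about 9% and over 99%, governed by the share of T2S off ULT and the agreement among users. The illustration treats each T2S patient as either off ULT or a user, with equal user agreement in both arms. The stronger claim that the analysis carries no information is not supported, since agreement remains useful within an arm. The primary intention-to-treat test and the sample size are unaffected.

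**What to change.** Change the analysis wording for this outcome:

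- Do not use the between-arm chi-squared or Fisher's exact test of ULT agreement as the adherence comparison.
- Keep self-report/refill agreement as a descriptive within-arm check of self-report, including for anti-inflammatory drugs.
- Report refill coverage against prescribed ULT over periods when ULT is prescribed: throughout in T2T, and after documented restart in T2S.
- Report separately the proportion of T2S patients with any ULT dispensed between the planned stop and documented restart.

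Prescription, self-report and refill data are already planned, so no new collection is needed. The cost is one planned between-group p-value, which would be hard to interpret in any case.
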